### Data management

All participant data will primarily be stored on a secure online database hosted by Research Electronic Data Capture (REDCap RCT). Each participant will also have a paper file that will be stored in a locked filing cabinet behind two locked doors. Files will be labeled with participant ID numbers and will not include the participant’s name. At a minimum, these paper files will include the following forms: original Participant Eligibility Checklist with a signed statement of eligibility by the Principal Investigator or Delegate; Medical Assessment Form; Nursing Assessment Form; baseline PHQ-9; Initial Assessment Checklist; Telephone Visit Checklist; In-Person Visit Checklist; Adverse Clinical Events Form; Concomitant Medication Record. All data captured on these paper forms will also be entered into the study’s secure online REDCap database. Additionally, in the case of technical difficulties precluding the use of the web-based database at the time of an in-person visit, necessary data will be collected on the appropriate paper forms, which will be entered into the REDCap database upon resolution of the technical difficulty. Any such paper assessment forms will be stored in the participant’s paper file as the source document. To document progress and research contact with each participant, a Research Note will be written in each participant’s electronic health record following each in-person study visit.

The original/paper signed consent form(s) will be stored in the “Consent Binder” in a locked cabinet, separately from other participant source documentation. A scanned copy of the consent form is uploaded to the participant’s electronic medical record (EMR).

### Monitoring

The study monitor will conduct monitoring visits at each site according to the following schedule: the Study Initiation Visit will occur at each site after obtaining all regulatory approvals (REB, NOL, etc.) but prior to enrolment of the first research participant; the first monitoring visit will be done after the first 5 participants have been enrolled at the site; the second monitoring visit will be done after an additional 20 participants have been enrolled at the site; additional monitoring visits will occur annually or after every 30 additional participants have been enrolled at the site, whichever comes first; the study closeout visit will be after the last participant has completed his/her involvement in the study (participant data not verified from previous visit should be completed during this visit). At each of these visits, the study monitor will review all of the source data in the CRF for 10% of the research participants. Should issues regarding data be observed during a monitoring visit, the data from all participants may be verified.

Since there are no early stopping rules or planned interim analysis and because the medication being investigated in the study is available on pharmacy shelves, a Data Monitoring Committee was deemed unnecessary.

### Outcome measures

#### Primary outcome measure

The primary outcome measure will be continuous abstinence from tobacco use during weeks 9–12 (as reported at clinic visits on weeks 10 and 13, and telephone interviews on weeks 11 and 12). Participants will be classified as abstinent if they respond “no” to both of the following questions: (i) “have you smoked any cigarettes (even a puff) in the last 7 days?” and (ii) “Have you used any tobacco product (i.e., chew, snuff, pipe, cigar, etc.) in the last 7 days?” Self-report will be biochemically confirmed with expired CO at each in-person visit and urinary anabasine at week 13.

#### Secondary outcome measures

The secondary outcome measures are self-reported continuous abstinence through week 9 to weeks 26 and 52, confirmed by urinary cotinine < 200 ng/ml (assay limit of detection) at the 26- and 52-week follow-up visits.

To test the hypothesis that rates of nicotine metabolism moderate the effect of patch titration, we will compare the quit outcomes in rapid versus slow nicotine metabolizers within and among the treatment groups.

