We hypothesize that a personalized dose of a nicotine patch will increase cessation rates relative to standard dosing based on the following empirical evidence. First, standard doses of a nicotine patch have low absolute efficacy due in part to inadequate replacement [11, 19]. Second, a fixed high-dose patch (44 mg) is no better than standard therapy in rapid metabolizers of nicotine unless there is a higher percent replacement of baseline nicotine levels [20, 21]. Third, using a nicotine patch prior to one’s target quit date (preloading), which allows for smoking concurrently with NRT, is safe and is associated with higher quit rates [22]. Fourth, our exploratory studies to date and clinical practice have indicated that titration with a nicotine patch up to 84 mg is associated with quitting completely or achieving a > 50% reduction confirmed by exhaled carbon monoxide (CO) readings, with reduced cravings and increased aversion to cigarettes [23]. Lastly, a nicotine patch has negligible abuse liability and dependence potential due to its slow onset and long duration of action [24]. Furthermore, clinical trials have shown that standard NRT doses are inadequate for rapid metabolizers of nicotine (i.e., those who inactivate nicotine to cotinine and then to 3-hydroxycotinine [3-HC] more quickly than others due to genetic variation affecting the activity of the hepatic enzyme CYP2A6) [20, 25]. A recent pilot study indicated rapid metabolizers may respond better to higher transdermal NRT doses [21]. Therefore, we aim to test a secondary hypothesis that baseline nicotine metabolite ratio (NMR) will moderate the experimental treatment effect, such that the benefit of dose titration will be greater in those participants who are rapid metabolizers of nicotine, and the final titrated dose they reach will be higher on average than the slow metabolizers. We further hypothesize that slow nicotine metabolizers will be more likely to quit on the standard 21 mg dose and stay in group C compared to rapid metabolizers. NMR will then be tested as a predictor of who will benefit most from the dose titration approach. This will be useful for optimization of treatment resources and cost effectiveness.

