### Initial assessment

At the initial assessment clinic visit (~ 3 h), written informed consent will be obtained from potential participants by the research analyst prior to any data acquisition. They will then complete a series of self-administered forms (Drug Abuse Screening Test [DAST-10] [26], Depression, Anxiety and Stress Scale [DASS 21] [27], Fagerström Test for Nicotine Dependence [FTND] [28], Alcohol Use Disorders Identification Test [AUDIT] [29], 36-Item Short-Form Health Survey [SF-36] [30, 31], Questionnaire of Smoking Urges - Brief [QSU-brief] [32, 33], Patient Health Questionnaire [PHQ-9] [34], Minnesota Nicotine Withdrawal Scale [MNWS] [35], and modified Cigarette Evaluation Questionnaire [mCEQ] [36]) and staff-administered forms (demographic questions, history of smoking and quit attempts, social exposure to smoking, substance use, medical history and medical assessment, including vital signs, height and weight and concomitant medication record). Participants will also undergo a physical examination, urine pregnancy test (if applicable; e.g., female, pre-menopause), and exhaled CO test and will provide a venous blood sample (10 ml) to assess 3-HC/cotinine ratio (NMR). The participant will provide an additional 10 mL of blood if they consented to the genetics sub-study. Participants may elect to take part in the genetics sub-study at any point during the study. The samples will be collected, processed (plasma aliquot, whole blood transferred to polypropylene tube), and stored in a freezer (acceptable freezing temperature − 80 to −20 °C) prior to being transported to the laboratory for analysis. Please see the SPIRIT checklist (Additional file 1) for all of the assessment and visit procedures.

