#### Analysis of secondary and tertiary outcomes

The proportion of patients who remain abstinent from week 9 to weeks 26 and 52 will be compared by logistic regression, weighted by the inverse probability of being included in the subset. Exploratory analysis of the role of nicotine metabolism on quit outcome will be performed: (1) initial analysis will compare the proportions of patients with rapid or slow NMR who achieve the primary outcome within each treatment group using a chi-square; (2) we will then conduct a post hoc analysis of NMR as a predictor or moderator of treatment outcome in the two treatment groups; and (3) an exploratory analysis of the correlation between final NRT dose given and NMR.

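### The moderation hypothesis is tested on rapid versus slow classes of a continuous metabolite ratio, which costs substantial power if the effect is graded; the scale of the later moderator analysis is not stated

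*Protocol article*

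**What the plan says.** Under Initial assessment, a baseline blood sample is taken "to assess 3-HC/cotinine ratio (NMR", a quantity on a continuous scale. Under Study objectives and hypothesis, the secondary hypothesis is that "baseline nicotine metabolite ratio (NMR) will moderate the experimental treatment effect", and the article adds that "NMR will then be tested as a predictor of who will benefit most from the dose titration approach".

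Two later places set the analysis:

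- Secondary outcome measures, for the moderation hypothesis: "we will compare the quit outcomes in rapid versus slow nicotine metabolizers within and among the treatment groups".
- Analysis of secondary and tertiary outcomes, which lists three exploratory steps:
  - Step 1 works by class: "initial analysis will compare the proportions of patients with rapid or slow NMR who achieve the primary outcome within each treatment group using a chi-square".
  - Step 2 turns to prediction and moderation, as a "post hoc analysis of NMR as a predictor or moderator of treatment outcome in the two treatment groups".
  - Step 3 looks at dose, through "an exploratory analysis of the correlation between final NRT dose given and NMR".

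The moderation comparison and step 1 therefore use two classes. Step 2 names NMR without saying whether it enters as a continuous variable or as classes. Step 3 mentions no split, but it concerns dose and not quit outcome.

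**The concern.** A split treats everyone on one side of the cut as alike. If the effect of NMR rises gradually, the split throws away part of what was measured, and both the predictor test and the moderator test lose power. Tests of effect modification are weak to begin with, and this trial has 200 participants per arm, a number chosen for the main effect. The result also comes to depend on where the cut falls.

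The practical risk is a null rapid-versus-slow comparison being read as evidence that NMR does not matter, when the measured values might have shown that it does. The article wants to use NMR to decide who should be offered titration, so a false null would defeat that aim.

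This point is about the scale on which NMR enters. It is separate from whether arms are compared within or between classes: a properly built interaction test would lose the same information if it used the two classes.

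**Working it through.** **The plan's own figure.** Sample size calculations gives 45% versus 30%, p = .05, 80% power and 163 per group. With a two-sided test and pooled variance:

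n = [1.960 × √(2 × 0.375 × 0.625) + 0.842 × √(0.45 × 0.55 + 0.30 × 0.70)]² / 0.15² = (1.342 + 0.569)² / 0.0225 ≈ 162.3, which rounds up to 163.

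The figure is reproduced. The planned 200 per group gives 87.5% power for the primary test. The article states no power for any NMR comparison.

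**Assumptions, none of them from the document.** Log NMR is about normal, its effect is linear on the logit scale, and the cut lies between the median and a quartile.

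**Information kept by a cut.** With a share q on one side of the cut and k the normal quantile of q, the share kept is φ(k)² / [q(1 − q)].

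| Cut | Calculation | Kept | Lost |
|---|---|---|---|
| 50/50 | 0.3989² / 0.25 | 0.637 | 36.3% |
| 70/30 | 0.3477² / 0.21 | 0.576 | 42.4% |
| 75/25 | 0.3178² / 0.1875 | 0.539 | 46.1% |

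In terms of the 400 randomized, the split is like analysing 400 × 0.637 ≈ 255 participants (median cut) or 400 × 0.539 ≈ 216 (75/25 cut).

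**Power after the cut.** This is Φ[(1.960 + z_power) × √kept − 1.960]. For a continuous test with 80% power:

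- Median cut: 2.802 × 0.798 − 1.960 = 0.276, so 60.8%.
- 75/25 cut: 2.802 × 0.734 − 1.960 = 0.096, so 53.8%.

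| Power, continuous | Median cut | Points lost | 75/25 cut | Points lost |
|---|---|---|---|---|
| 30% | 20.8% | 9.2 | 18.2% | 11.8 |
| 50% | 34.6% | 15.4 | 30.1% | 19.9 |
| 80% | 60.8% | 19.2 | 53.8% | 26.2 |
| 90% | 73.4% | 16.6 | 66.2% | 23.8 |
| 95% | 82.0% | 13.0 | 75.3% | 19.7 |

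**Check by simulation.** Logistic data were generated with abstinence of 30% and 45% at mean NMR.

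- Arm-by-NMR interaction, 400 participants, 0.6 log-odds per SD, 500 runs: 81% continuous against 60% (median cut), and 82% against 55% (75/25 cut).
- Within one arm of 200 at 30% abstinence, 0.45 log-odds per SD, 600 runs, continuous logistic model against the chi-square of step 1: 81% against 61% (median cut), and 79% against 56% (75/25 cut).

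Both agree with the closed form within simulation error of about 2 points. The loss therefore applies to an interaction test and to the within-group chi-square alike.

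**Direction of the caveat.** The share kept is the squared correlation between the continuous value and the class, and it is symmetric. If the true relation were a step exactly at the cut, the continuous test would be the weaker one by a similar amount.

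**The case against.** The strongest reply is step 2. It is the only step labelled a moderator analysis, it follows step 1 by design, and it speaks of NMR rather than of rapid or slow NMR. A reader might infer that every quit-outcome analysis of NMR uses two classes. The document does not support that, because step 2 could be continuous as written. What stands against the reply is that step 2 is labelled post hoc, while Secondary outcome measures names the rapid/slow comparison as the way to test the hypothesis.

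A reader might also take the percentages as properties of this trial. They are not. They depend on an assumed distribution, an assumed linear effect, an assumed cut and the power the continuous test would have. Across the cuts and starting powers tabulated, the loss runs from about 9 to 26 points.

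Nor is the missing cut value itself a fault. An article may leave it to the analysis plan, and whether the cited metabolism trials support a threshold cannot be judged here. The point does not need the cut value, since any cut loses information when the effect is graded.

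Finally, the hypotheses are worded by class, the analyses are called exploratory, and a class comparison is easy to read. All of this is fair, and it supports keeping the class table as a display. It does not make two classes the better test. The article's rationale is itself graded: speed of inactivation and percent replacement of nicotine. If slow metabolizers quit more often in the run-in, as the article expects, a cut set outside the randomized sample could also divide it unevenly, and uneven cuts keep less.

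**Conclusion.** The point holds in a limited, conditional form. The article chooses an inefficient scale for the stated test of moderation and for step 1, and it leaves the scale of step 2 open. Given approximate normality of log NMR, linearity on the logit scale and a cut between the median and a quartile, 36-46% of the information is lost. Against a continuous test with 80% power that means about 19-26 points, and against one with 30% power about 9-12 points. A true step effect at the cut would reverse the ranking, and nothing in the article states such a threshold.

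The consequence is confined to a secondary hypothesis that the analysis section treats as exploratory. The article should be changed on this point, but the trial's main conclusion does not depend on it.

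**What to change.** In Secondary outcome measures, and in step 2 of Analysis of secondary and tertiary outcomes, define the moderation test as the interaction of arm with continuous log NMR in a logistic model of the primary outcome. Enter log NMR as continuous in the predictor analysis too. Add a spline term as a check on linearity, and present the difference in abstinence between groups A and B across the NMR range. Keep the rapid/slow comparison of step 1 as a descriptive display, at a cut stated in advance.

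The cost is wording only. The ratio is already planned at the initial assessment, so no participants, visits or assays are added. The downsides are the linearity assumption, which the spline checks, and a summary slightly less simple than two classes.

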### Statistical analysis

Descriptive statistics will be used to summarize baseline characteristics. Baseline characteristics will be examined for any statistically significant differences between randomized groups. Such variables will be used as covariates in an adjusted analysis. The primary analysis will follow the intention-to-treat principle (ITT) [40] whereby all participants that drop out of the study or are otherwise lost-to-follow-up will be classified as still smoking. The primary analysis will compare the proportions of patients in each group (group A vs group B) to achieve smoking cessation using Pearson’s chi-square test. Additional analysis will employ logistic regression to adjust for variables known to be strongly associated with smoking cessation, including but not limited to age, sex, and psychiatric comorbidities.

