### Titration phase (weeks 3–7)

Participants in groups A and B will receive an active nicotine patch (21 mg/day) for the entire titration phase in addition to escalating doses of either active patches (group A) or placebo patches (group B) per the following dose titration protocol. The nicotine patch will be dispensed weekly during this titration phase, with dose adjustments made by the study physician at each weekly study visit based on tolerability and the average number of cigarettes smoked per day (CPD) in the preceding week (see Table 1 for the dosing algorithm based on amount of continued smoking). If adverse effects are experienced at a given dose, a dose reduction back down to a previously tolerated dose will be permitted as determined by the study physician.

**Table 1 Tab1:** Algorithm for weekly dose titration based on amount of smoking during the previous week

If participant reports smoking…	Add this patch to current dose
0 cigarettes	Continue with last weeks’ dose
1–5 cigarettes per day	Add 7 mg patch (or placebo) to last week’s dose
6–9 cigarettes per day	Add 14 mg patch (or placebo) to last week’s dose
10 or more cigarettes per day	Add 21 mg patch (or placebo) to last week’s dose

Group C will continue to visit the clinic on a bi-weekly basis (weeks 3, 5, and 7) and receive 21 mg/day of a nicotine patch, and telephone follow-up visits in the intervening weeks (weeks 4 and 6). No short-acting NRT will be permitted for any participant. Participants will be contacted by telephone 1 to 2 days in advance of their scheduled clinic visits during the titration phase to remind them of their upcoming appointment.

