#### Sample size calculations

The anticipated absolute continuous abstinence rate for group A (weeks 9 to 12) for the primary outcome measure is set at 45%. This is based on the quit rates reported for combination NRT (nicotine patch and short-acting NRT) [16]. Trials of combination NRT were used to inform this estimate because: (1) randomized trials of a high-dose nicotine patch are not available to inform the projected treatment size, and (2) similar to nicotine patch, combination NRT also allows upward titration to reach satiety. It is anticipated that the abstinence rates for an active titrated nicotine patch will at least meet, if not exceed those of combination NRT. The estimated continuous abstinence rates during weeks 9 to 12 for group B are 30% based on published literature of the effects of a standard nicotine patch in clinical trials [41]. Assuming *p* = .05, a sample of 163 per group provides 80% power to detect this difference at weeks 9 through 12. With an estimated 20% quit rate during the 2-week run-in period, we therefore plan to recruit approximately 500 participants into the trial until we have 400 eligible for randomization. Randomized groups of 200 participants per group will ensure that the group is adequately powered for longer-term outcomes as well. Since we are using ITT, all participants randomized to a treatment arm will be included in the analysis so our *n* will remain constant and our power to detect a difference between groups should not be significantly affected by loss to follow-up as long as it is more or less equal in the two arms. Our overall proportion of participants defined as quit will decrease but the difference between the two groups should remain the same.

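### Choosing covariates by baseline significance tests lets chance imbalance decide the supportive adjusted analysis; the primary chi-square test is unaffected

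*Protocol article*

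**What the plan says.** The Statistical analysis section of the protocol article contains three statements that bear on this point.

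- Covariates by baseline test: "Baseline characteristics will be examined for any statistically significant differences between randomized groups. Such variables will be used as covariates in an adjusted analysis".
- Primary analysis: the proportions abstinent in groups A and B are compared with Pearson's chi-square test. There is no adjustment, and dropouts are counted as smokers.
- Covariates by prognosis: a further logistic regression will "adjust for variables known to be strongly associated with smoking cessation, including but not limited to age, sex, and psychiatric comorbidities".

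The article does not say whether the first and third statements describe two adjusted analyses or two ways of filling one model. It also does not say how many baseline characteristics will be tested.

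**The concern.** A baseline test between randomised arms asks whether the difference could be due to chance. If allocation was sound, the answer is already known: it is. The test therefore carries no information about whether a variable matters for quitting. What makes a covariate worth including is its association with the outcome, and the rule does not look at that.

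Three consequences follow for the adjusted analysis. A strong predictor that could enter only through this rule will usually be absent. A variable unrelated to quitting has the same chance of entering as a strong one. The content of the model is fixed only after the data have been seen, so the odds ratio it yields is conditional on a set of variables that nobody could have named in advance. If the adjusted and unadjusted results differ, the reader has a harder task in saying why.

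**Working it through.** **Inputs from the article.** Abstinence 45% in group A and 30% in group B, "a sample of 163 per group provides 80% power", and 200 per group planned (Sample size calculations); 1:1 randomisation in permuted blocks (Randomization). The significance level is .05; sidedness is not stated, and two-sided is assumed.

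**Inputs assumed.** The number of baseline variables tested (k), their independence, and the strength of the predictor. None is given in the article, so ranges are shown.

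**1. The plan's own figure.** With mean proportion 0.375 and no continuity correction:

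n = [1.960 × √(2 × 0.375 × 0.625) + 0.842 × √(0.45 × 0.55 + 0.30 × 0.70)]² / 0.15²
= [1.342 + 0.569]² / 0.0225 = 162.3, so 163 per group.

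This matches the article and supports the two-sided reading (a one-sided test would need 128).

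**2. Power of the unadjusted test at the planned size.** z = (0.15 × √200 − 1.342) / 0.676 = 1.152, which gives 87.5%. The same formula gives 80.2% at 163 per group.

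**3. What the rule selects.** Each variable is selected with probability 0.05, prognostic or not. The chance that at least one of k independent variables is selected is 1 − 0.95^k:

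| k | 5 | 10 | 15 | 20 |
|---|---|---|---|---|
| At least one selected | 23% | 40% | 54% | 64% |

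**4. What the rule does to the adjusted analysis.** Simulation: 4,000 trials per setting, 200 per arm, 15 independent baseline variables of which one predicts quitting, marginal rates held at 30% versus 45% (or 30% in both arms for the null). Three analyses were compared: the chi-square test, logistic regression on whichever variables differed at p < .05, and logistic regression on the one predictor, prespecified. The table gives the percentage of trials rejecting.

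| Log-odds ratio per SD (assumed) | Chi-square | Significance-selected | Prespecified |
|---|---|---|---|
| 0.4, 30% v 45% | 88.0 | 87.8 | 89.2 |
| 0.7, 30% v 45% | 88.0 | 87.9 | 90.9 |
| 1.0, 30% v 45% | 87.6 | 88.3 | 92.5 |
| 0.4, null | 5.4 | 5.5 | 5.6 |
| 0.7, null | 5.2 | 4.9 | 5.3 |
| 1.0, null | 4.9 | 4.8 | 5.1 |

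The true predictor was selected by the rule in 4.8% to 5.4% of trials, so it was left out of about 95%. The gain from prespecifying it is 89.2 − 88.0 = 1.2, 90.9 − 88.0 = 2.9 and 92.5 − 87.6 = 4.9 points. The significance rule changes power by −0.2, −0.1 and +0.7 points. The simulation error of one power figure is about √(0.88 × 0.12 / 4000) = 0.5 points.

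**The case against.** The strongest reply is that little depends on the rule. The primary test is fixed in advance and unadjusted, and the same section already plans a logistic regression on known predictors of quitting. Most of this stands, and it rules out several stronger readings that a reader might infer.

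- **That the primary result or the error rate is compromised.** It is not. The rule feeds only an adjusted analysis, rejection under the null stayed at 4.8% to 5.6% for all three methods, and 163 and 200 per group do not depend on it. A reader can still rely on the chi-square test if the results differ.
- **That the plan ignores prognostic factors.** It does not. Age, sex and psychiatric comorbidities are named on prognostic grounds. The 95% omission applies only to predictors that would have to enter through the significance rule.
- **That the open wording, "including but not limited to age, sex, and psychiatric comorbidities", is an error in itself.** Closing such a list, and naming site or nicotine dependence in it, is commonly left to the full analysis plan, which is not shown.
- **That the gain in power is much larger.** The planned marginal odds ratio is (0.45/0.55)/(0.30/0.70) = 1.91. Using about 1.9 as a conditional odds ratio with a covariate of 0.8 per SD implies about 30% versus 43% and 77% unadjusted power. That is a smaller effect than the planned one, and it inflates the apparent gain.
- **That smoking before allocation drives the dosing rule as a whole.** Titration uses "the average number of cigarettes smoked per day (CPD) in the preceding week" at each weekly visit. At most the week 3 step reflects the run-in; later steps reflect smoking after randomisation.

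One part of the reply fails. The significance-test rule is an explicit instruction, not a detail lost when the protocol was condensed, and the prognostic regression stands beside it without replacing it.

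**Conclusion.** The point holds in a limited form. The section states a covariate rule that selects chance imbalance, takes no account of prognosis and leaves an adjusted model undefined until the data are in. The damage is confined to supportive analysis.

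The size is modest: about 1 to 5 points of power in the adjusted analysis, if one predictor has a log-odds ratio of 0.4 to 1.0 per SD. Deleting the rule does not by itself recover this; prespecifying the predictor does, and then only for the adjusted analysis, since the primary test remains unadjusted. That about 5% of variables enter follows from randomisation and the .05 level (itself assumed for the baseline tests). The 23% to 64% chance that at least one enters depends further on how many are tested and on their independence; correlated questionnaire scores would lower it.

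The rule should be corrected because it is stated outright and the remedy is nearly free.

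**What to change.** Delete the two sentences that test baseline characteristics between arms and turn the significant ones into covariates. Baseline characteristics can still be summarised by arm, without tests.

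Keep one adjusted logistic regression, on the prognostic principle that the section already states. Fix its covariates before unblinding, from data recorded before randomisation: the three named (age, sex, psychiatric comorbidities) plus, for example, site, FTND and baseline cigarettes per day. Nicotine metabolite ratio already has its own exploratory analyses as predictor and moderator and need not be in this list. Report the single adjusted estimate beside the chi-square result, and state that the chi-square test remains primary.

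The cost is wording. Two sites, FTND and smoking history are already part of the design and the initial assessment, so no visit, measurement or participant is added. The Trial status section expects recruitment to run to January 2022, so when the article appeared in June 2020 there was time to make the change before unblinding.
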